The second hypothesis is that COAST+EF and COAST+EF/IF will yield greater improvements in patient insomnia symptom severity than COAST only over the acute 6-week intervention period. We will compute the change in ISI from baseline to 6 weeks (∆ISI = baseline ISI − 6-week ISI), with higher ∆ISI values indicating a greater improvement over time. We will use a mixed effects model to regress ∆ISI on group, accounting for nesting within providers through a random effect and including relevant covariates. We will extract estimates from the model to compute the standardized mean difference *d* [70, 71] and 95% confidence interval between COAST and COAST+ (EF; EF/IF) accounting for patients nested within providers. Second, using a mixed effects model with a random clinician effect, we will regress ISI at baseline and 6 weeks of treatment (COAST versus COAST+EF and COAST+EF/IF), time, and their interaction, controlling for relevant covariates. A significant treatment-by-time effect will indicate that the change in ISI differs between COAST and COAST+EF and COAST+EF/IF. Assuming an average of 12 providers per group (8 in COAST and 16 in COAST+EF and COAST+EF/IF) and 36 patients per clinician, we expect 0.80 power (alpha = 0.05) to detect a standardized mean difference of 0.232 between groups. We will also evaluate the extent to which COAST+EF is not inferior to COAST+EF/IF as measured by changes on the ISI over the acute 6-week intervention period. This non-inferiority hypothesis will be tested with the general form—H_0_: COAST+EF is inferior to COAST+EF/IF versus H_1_: COAST+EF is non-inferior to COAST+EF/IF. Using the methods described above, we will compute the standardized mean difference *d* and 95% confidence interval [*d* (95% CI)] for COAST+EF − COAST+EF/IF of ∆ISI. As positive values of ∆ISI indicate more improvement, a positive *d* is in favor of COAST+EF and a negative *d* is in favor of COAST+EF/IF. We will use a non-inferiority margin (NIM) of − 0.50 and declare COAST+EF to be non-inferior to COAST+EF/IF if the lower bound of the 95% CI for *d* is > − 0.50. We will declare COAST+EF to be inferior to COAST+EF/IF if the lower bound of the 95% CI for *d* is ≤ − 0.50. For example, if *d* (95% CI) = − 0.10 (− 0.40, 0.20), we would declare COAST+EF as non-inferior to COAST+EF/IF because − 0.40 > − 0.50. However, if *d* (95%CI) = − 0.40 (− 0.70, − 0.10), we will declare COAST+EF to be inferior because − 0.70 ≤ − 0.50. These one-sided decision rules equate to requiring the effect size of the COAST+EF to COAST+EF/IF comparison to have no more than moderate strength (|d| = 0. 5), in favor of COAST+EF/IF. The NIM of |d| = 0.5 set to determine non-inferiority is stringent as it represents 50% of the effect size reported in recent meta-analyses [50, 72, 73]. Assuming 8 providers per group and 36 patients per clinician, an intra-class correlation of 0.01 [74], a non-inferiority margin of 0.50, and a true difference of δ = 0, we expect > 0.99 power to reject our null hypothesis and conclude that COAST+EF is non-inferior to COAST+IF/EF.

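### A failed non-inferiority test of COAST+EF against COAST+EF/IF is to be declared as inferiority, with no outcome for non-inferiority not shown

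*Protocol article*

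**What the plan says.** The rule is in the section Statistical analyses plan and power calculations, under the second hypothesis. *d* is the standardized difference in ISI improvement, COAST+EF minus COAST+EF/IF, so negative values favour COAST+EF/IF.

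- Hypotheses, null first: "COAST+EF is inferior to COAST+EF/IF versus H_1_: COAST+EF is non-inferior to COAST+EF/IF".
- Margin: "We will use a non-inferiority margin (NIM) of − 0.50".
- Non-inferiority is declared if the lower 95% bound is above −0.50. The first example, *d* = −0.10 (−0.40, 0.20), reads: "we would declare COAST+EF as non-inferior to COAST+EF/IF because − 0.40 > − 0.50".
- Inferiority: "We will declare COAST+EF to be inferior to COAST+EF/IF if the lower bound of the 95% CI for" *d* is at or below −0.50. The second example, *d* = −0.40 (−0.70, −0.10), reads: "we will declare COAST+EF to be inferior because − 0.70 ≤ − 0.50".
- Precision: "Assuming 8 providers per group and 36 patients per clinician, an intra-class correlation of 0.01". With a true difference of 0, power above 0.99 is claimed.

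The upper bound plays no part in either rule, and the section gives no third outcome.

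**The concern.** A lower bound at or below −0.50 means that the data have not ruled out a deficit as large as the margin. It does not mean that they have shown one. Under the plan's hypotheses that is failure to reject the null, yet the rule reports the null as true. Showing inferiority by the margin would need the upper bound to lie below −0.50.

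The second example shows that this is a rule and not loose phrasing. Its estimate (−0.40) and upper bound (−0.10) both lie inside the margin, so the interval is compatible with non-inferiority as the plan defines it.

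Two things are at stake. First, the less precise the trial turns out to be (lost providers, missing ISI scores, a larger ICC), the more often COAST+EF is declared inferior when it is within the margin. Second, the Trial design section expects the results to feed directly into policy and practice guidelines. An unsupported inferiority label could push sites towards the strategy that also needs a local champion.

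**Working it through.** **Inputs, all from the section named above.** 8 providers per arm; 36 patients per provider; ICC 0.01; margin −0.50; two-sided 95% CI, so one-sided 0.025 on the lower bound.

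**1. The plan's own figure.**

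- Patients per arm: 8 × 36 = 288.
- Design effect: 1 + (36 − 1) × 0.01 = 1.35.
- Effective patients per arm: 288 / 1.35 = 213.3.
- SE(*d*) = √(2 / 213.3) = 0.0968.
- Power at a true difference of 0: 0.9993 (normal) or 0.998 (noncentral t, 16 − 2 = 14 df).

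The stated power above 0.99 is reproduced.

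**2. What the rule does at that precision.** The CI half-width is 2.145 × 0.0968 = 0.208 (t, 14 df), or 1.960 × 0.0968 = 0.190 (normal). With the t interval:

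- Lower bound above −0.50 needs an estimate above −0.50 + 0.208 = −0.292.
- Upper bound below −0.50 needs an estimate below −0.50 − 0.208 = −0.708.
- Between −0.708 and −0.292, neither non-inferiority nor inferiority by the margin is shown. The written rule calls this whole zone inferior.

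**3. How often.** P(declared inferior) = P[(estimate + 0.50)/SE ≤ t], from the noncentral t with noncentrality (true *d* + 0.50)/SE. The last column is the chance that the upper bound is below −0.50 (t version).

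| True *d* (all inside the margin) | Declared inferior, t | Declared inferior, normal | Upper bound < −0.50 |
|---|---|---|---|
| 0 | 0.002 | 0.0007 | < 0.0001 |
| −0.25 | 0.33 | 0.27 | < 0.0001 |
| −0.30 | 0.51 | 0.46 | < 0.0001 |
| −0.40 | 0.84 | 0.82 | 0.002 |

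**4. Sensitivity to precision.** The ICCs of 0.05 and 0.10 are assumptions; the plan gives only 0.01. Numbers of providers and patients are kept as planned, and true *d* = 0.

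| ICC | Design effect | SE | Half-width (t) | Declared inferior (t) |
|---|---|---|---|---|
| 0.01 | 1.35 | 0.097 | 0.208 | 0.002 |
| 0.05 | 2.75 | 0.138 | 0.296 | 0.08 |
| 0.10 | 4.50 | 0.177 | 0.379 | 0.25 |

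The plan's two illustrative intervals have a half-width of (0.20 + 0.40)/2 = 0.30. At that precision (normal, SE = 0.30/1.96 = 0.153) inferiority is declared in 9.6% of trials at true *d* = 0 and in 50% at −0.20. At −0.20, 24% of all trials would be declared inferior with an interval that also includes 0.

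**The case against.** The opposing case does not defend the rule's logic. It concerns how much the error matters, and several of its points stand.

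- **At planned precision the result is not empty.** With a half-width of 0.208, an interval whose lower bound is at −0.50 has its upper bound at −0.50 + 2 × 0.208 = −0.08 (−0.12 with the normal interval), so it excludes 0. The plan's second example does too. Such a result shows COAST+EF to be worse than COAST+EF/IF, though not by the margin. It is inconclusive only relative to the margin. An interval covering both −0.50 and 0 needs a half-width above 0.25. That takes an ICC of roughly 0.03 to 0.04 at full enrolment, or a shortfall in providers or patients.
- **Extreme illustrations are remote.** A result such as 0.00 (−0.55, 0.55) would be labelled inferior, but at 8 × 36 per arm it needs an ICC of about 0.24. It shows the logic and is not a likely outcome.
- **The probabilities do not change with the fix.** The 0.33 and 0.51 are the chances of missing non-inferiority at those true values. A corrected rule changes the label on those trials, not their number.
- **The interval will be available.** The plan commits to computing *d* with its 95% CI, so a careful reader could see past the label. The design also gives first place to the implementation outcomes.

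These points limit the consequence but do not rescue the rule. The margin defines inferiority in the plan's own null hypothesis, and failing to reject that null cannot establish it. If the intended meaning is merely worse than COAST+EF/IF, the condition would be an upper bound below 0, and the plan does not use that either.

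**Conclusion.** The rule is wrong as written. It is stated explicitly and repeated in a worked example, so it is not a detail left to a fuller document. It turns failure to show non-inferiority into a declaration of inferiority.

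At the planned size and ICC, COAST+EF would be declared inferior with probability 0.33 at a true *d* of −0.25 and 0.51 at −0.30, although both are non-inferior by the plan's margin. These figures assume a t interval on 14 df; the normal version gives 0.27 and 0.46. At a true *d* of 0 the risk is negligible at ICC 0.01 (0.002). It rises to 0.08 or 0.25 only if the ICC is 0.05 or 0.10, which are assumed values. The estimate, the sample size and the properties of the non-inferiority test itself stand.

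**What to change.** Replace the two-way rule with three outcomes for the 95% CI of *d* (COAST+EF minus COAST+EF/IF):

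1. Lower bound above −0.50: COAST+EF is non-inferior.
2. Upper bound below −0.50: COAST+EF is inferior by more than the margin.
3. Otherwise: non-inferiority not shown. Within this outcome, state separately whether the upper bound is below 0, which shows COAST+EF/IF to be better, though not by the margin.

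Reword the second example so that *d* = −0.40 (−0.70, −0.10) reads as non-inferiority not shown, with COAST+EF/IF better because the upper bound is below 0.

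The cost is wording only. No data, patients or recalculation of power are needed, because the condition for declaring non-inferiority is the same as now. The change should be made before the randomization is unmasked.

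### The non-inferiority margin is fixed only in SD units of the trial's own data, so its size in ISI points is unknown in advance and grows with outcome variability

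*Protocol article*

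**What the plan says.** All of this stands in the protocol article, section Statistical analyses plan and power calculations. The non-inferiority hypothesis concerns COAST+EF against COAST+EF/IF "as measured by changes on the ISI over the acute 6-week intervention period". For the effect size the section says: "We will extract estimates from the model to compute the standardized mean difference", with a 95% confidence interval. Negative d favours COAST+EF/IF. Non-inferiority is declared if the lower bound lies above −0.50, and two worked examples on the d scale illustrate the rule.

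Two sentences explain the choice of 0.50. One translates it into a strength of effect: "These one-sided decision rules equate to requiring the effect size of the COAST+EF to COAST+EF/IF comparison to have no more than moderate strength". The other relates it to published effects: "The NIM of |d| = 0.5 set to determine non-inferiority is stringent as it represents 50% of the effect size reported in recent meta-analyses".

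The power statement reads "Assuming 8 providers per group and 36 patients per clinician, an intra-class correlation of 0.01", then "a non-inferiority margin of 0.50, and a true difference of" zero, giving more than "0.99 power to reject our null hypothesis and conclude that COAST+EF is non-inferior".

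The article gives no margin in ISI points, no assumed SD of ISI change and no external reference SD. The standardizing SD is not named beyond the reference to model estimates and two cited methods.

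**The concern.** A non-inferiority margin says how much worse the leaner strategy may be and still count as acceptable. For a patient or a clinic director that is a number of ISI points, and the article itself reads the ISI in points in its Background, where it uses cutoffs of 15 and 8. Under the stated rule the tolerated number of points is not known until the data are in, because it is 0.50 times an SD estimated in this trial.

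The direction also matters. A larger SD shrinks d for a given point deficit, while the width of the interval for d hardly changes. The same deficit therefore becomes easier to pass as outcomes become more variable, whereas in a non-inferiority comparison noise should make the claim harder to establish. At stake is hypothesis 2(b), which bears on whether internal facilitation adds patient benefit over external facilitation alone.

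**Working it through.** **Inputs from the article:** 8 providers per arm, 36 patients per provider, ICC 0.01, margin 0.50, true difference 0, and a two-sided 95% CI (one-sided 0.025). **Assumed:** an SD of ISI change of 4 to 8 points, because the article states none.

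**Step 1: reproduce the stated power.**
- Patients per arm: 8 × 36 = 288. Design effect: 1 + 35 × 0.01 = 1.35. Effective n: 288 / 1.35 = 213.3.
- SE(d) = √(1.35 × 2 / 288) = 0.0968.
- Power at zero difference = Φ(0.50 / 0.0968 − 1.96) = Φ(3.20) = 0.9993. With a noncentral t on 14 df it is 0.998.

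The stated figure is correct. SE(d) does not depend on the SD in points. Estimating the SD adds only about 0.25 / (2 × 576) = 0.0002 to a variance of 0.0094 at d = −0.50, and this is ignored below.

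**Step 2: put the margin and a true 2-point deficit in ISI points.** The margin is 0.50 × SD. The pass probability under the article's rule is Φ((0.50 − 2/SD) / 0.0968 − 1.96). For comparison, a margin fixed at 3 points (for illustration only; it equals 0.50 × 6) gives Φ((3 − 2) / (SD × 0.0968) − 1.96).

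| Assumed SD | Margin in points | Pass probability, article's rule | Pass probability, fixed 3-point margin |
|---|---|---|---|
| 4 | 2.0 | 0.025 | 0.73 |
| 5 | 2.5 | 0.18 | 0.54 |
| 6 | 3.0 | 0.41 | 0.41 |
| 7 | 3.5 | 0.60 | 0.31 |
| 8 | 4.0 | 0.73 | 0.25 |

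With t on 14 df the article's rule gives 0.025 / 0.16 / 0.36 / 0.54 / 0.67, which is the same pattern.

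**Step 3: the same thing for an observed deficit.** The half-width of the interval for d is 1.96 × 0.0968 = 0.190, so the largest observed deficit that passes is d = −0.310. An observed deficit of 2.0 points has lower bound −2/6 − 0.190 = −0.523 at SD 6 and fails. At SD 7 the bound is −2/7 − 0.190 = −0.475 and it passes.

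**Step 4: power at zero difference for a fixed margin.** Φ(3 / (SD × 0.0968) − 1.96) for a 3-point margin is above 0.999 at SD 6, 0.993 at SD 7 and 0.97 at SD 8 (0.95 with t on 14 df).

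**The case against.** The rule is fully pre-specified and internally valid. The null is d ≤ −0.50, and the one-sided error at that boundary is about 0.025 whatever the SD. A 2-point deficit at SD 8 is d = −0.25, inside the margin, so passing it is a correct decision under the rule as written. A reader might take the table as showing an inflated false-positive rate. It does not: the article nowhere says that 2 points is unacceptable. This part of the objection stands.

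It also stands that a fixed margin does not free the verdict from noise. The last column of the table moves just as far. What changes is the direction.

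The standardized unit has a reason: the margin is tied to published effect sizes, which are on that scale, and the superiority calculation uses it too. A reader might go on to infer that the SD here differs from the one used in those meta-analyses, so that the 50% claim fails. The article does not show how the cited studies standardized, nor any pre-post correlation, so this cannot be concluded. Whether 0.50 is too wide is a separate question.

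A reader might further infer that the rule rewards poor trial conduct. The likely sources of variability, such as few exclusions and providers free to modify recommendations, are deliberate features of a pragmatic design, and no figure shows how far they raise the SD.

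Finally, the exact standardizer may be set out in an analysis plan that is not shown. That would settle which model-based SD is used. Unless it also fixed a reference SD or a margin in points, the margin would still move with the data.

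**Conclusion.** The point holds in limited form. The arithmetic, the power figure and the type I error on the d scale are sound; the weakness is the scale on which the decision is taken. The margin in ISI points is left to the observed SD, and greater variability makes a given point deficit easier to call non-inferior. Over an assumed SD of 4 to 8 the margin doubles, from 2.0 to 4.0 points, and the chance that a true 2-point deficit passes rises from about 0.03 to about 0.73.

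These sizes rest on the assumed SD range, the planned 8 × 36 per arm and ICC 0.01. The direction does not depend on the SD range. The conclusion takes the article at its word that d is computed from this trial's model estimates. It is worth correcting because the correction is cheap and decides which deficits can be called non-inferior.

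**What to change.** Before unmasking, state the margin once in ISI points. Justify it either directly on the ISI scale or as the chosen standardized margin times a reference SD fixed in advance from a named external source. The sponsor's earlier 27-person sample is too small to serve alone: a 95% interval for an SD from 27 people runs from about 0.79 to 1.37 times the estimate (√(26/χ²) at the 97.5% and 2.5% points of χ² on 26 df), so a nominal 3-point margin could stand for 2.4 to 4.1 points.

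Base the decision on the 95% CI for the adjusted mean difference in ISI change from the same mixed model, and report d with its interval descriptively. Restate power for the chosen margin over a range of SDs, as in step 4.

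The cost is a change of wording; model and data collection stay as they are. The downside is that the power figure then depends on the SD and may be slightly less favourable than the present value above 0.99.

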
## Secondary and exploratory analyses

Secondary analyses will explore the durability of symptom improvements over time among patients who used the COAST platform with their provider over time. While the time elapsed between the post-treatment at 6 weeks and discharge may vary across patients, we will, nevertheless, explore the extent to which detectable sleep improvements after 6 weeks may persist over time. The variability in elapsed time between the post-treatment and discharge assessment will be taken into consideration in the statistical analyses. We will first summarize and compare the differences in discharge times by examining relevant baseline characteristics (e.g., symptom severity, sleepiness, daytime impairments). We will then compute the average rate of change in ISI score per month [(6-week ISI − discharge ISI)/(discharge week − 6)]. Using a mixed model, we will fit an intercept-only model for the rate of change in ISI score, accounting for nesting within clinician through a random effect. An intercept that differs significantly from zero will indicate further change in ISI score between 6 weeks and discharge. Models will also include age and sex and other baseline characteristics that may be found to impact time to discharge. Finally, we will explore whether change in psychological distress (e.g., PHQ-8, GAD-7, PCL-5) corresponds to use of COAST by computing correlations between change in ISI score, and number of interactions with their assigned coach.

While the study is not powered for definitive determination of the effects of each of the clinician characteristics on implementation measures or patient outcome data, we will complete exploratory analyses to evaluate if these variables may impact outcomes of interest to inform future implementation efforts.

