Prior to the enrollment of providers and patients, the NOCTEM team and the EFs and IFs will first complete an in-depth review of written guidelines and standard operating procedures for this project. During the trial, the EF and IF teams will meet monthly by phone and communicate via email, as needed, between scheduled monthly meetings to address any issues that arise and share newly acquired information. The EF and IF guidelines will be updated as needed to make sure both processes are documented and kept up to date during the trial.

The sleep intervention is the same for all patients enrolled by participating clinicians. When a disordered sleep pattern is detected by the NOCTEM algorithms (usually within 7 days), the provider will receive automated sleep recommendations for each patient and will be asked to review and confirm prior to forwarding it to the patient. Recommendations are consistent with stimulus control, sleep restriction, and other EB-BSM techniques, including suggested times for rise time and bedtime and exercise to minimize nightmares. Providers may elect to modify the algorithm-driven recommendations as they see fit, based on knowledge of their patients. Patients will receive their provider-approved, personalized behavioral sleep recommendations on a weekly basis. This process will be repeated for the next 4 to 6 weeks.

Participating patients will not be terminated from the study until (1) they decide to stop using the app; or (2) their provider deems that a different treatment or referral is required; or (3) the treatment course is complete, and the use of the app is no longer necessary; or (4) the end of the project. COAST is not commercially available, and patients who wish to remain in sleep treatment will be encouraged to discuss options with their provider. Because the COAST system requires that a provider monitors entries and sleep status and progress, the app will be disabled when a patient is no longer in the care of a provider. This will avoid misleading patients that they are still under the care of the provider through the app only.

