**Assessments:**							
Demographics and practice survey			X				
Post-training survey			X				
Organization readiness for implementing changes			X			X	X
System usability scale			X	X		X	X

Fidelity is evaluated by quantifying the adherence (or discrepancy) between algorithm-recommended interventions relative to interventions that are sent to patients by providers. As in some cases there may be valid clinical reasons why a provider determines a patient should not receive the algorithm-recommended intervention (e.g., sickness, incompatible with assigned duties), we expect a rate of non-adherence of approximately 20%—noting we will not be accessing patients medical records to validate the potential reasons for deviations.

The primary patient-centered outcome measure of treatment effectiveness is the Insomnia Severity Index (ISI [32]). Other symptom domains to be assessed are summarized in Table 3, and include the PTSD Checklist-5 (PCL-5 [47, 48]), the 8-item Patient Health Questionnaire (PHQ-8 [49]) to assess symptoms of depression, the 7-item Generalized Anxiety Disorder scale of the PHQ (GAD-7 [50]), the PEG, a 3-item validated and reliable pain measure [68], and the 4-item PROMIS Satisfaction with Social Roles and Activities [69]. For patients, the total time required to complete the battery is approximately 20 min. The battery will be completed through the NOCTEM app at baseline, post-treatment, and again 3 and 12 months post-treatment.

**Table 3 Tab3:** Self-report measures of sleep and daytime symptoms to be completed by participating patients at baseline, post-intervention, and at the follow-up assessments

Domain	Scale	Number of items	Time to complete

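### The durability rate is labelled monthly but computed per week, has no rule for discharge at or before week 6, leaves the tested intercept unclear, and uses a discharge ISI that is not in the assessment schedule

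*Protocol article*

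**What the plan says.** The section Secondary and exploratory analyses fixes the measure, the model and the test for whether sleep gains last.

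- **Measure.** "We will then compute the average rate of change in ISI score per month", with the formula "6-week ISI − discharge ISI)/(discharge week − 6" (outer brackets omitted here).
- **Timing.** The section accepts variable follow-up ("While the time elapsed between the post-treatment at 6 weeks and discharge may vary across patients"), and says that this variability will be taken into account and that discharge times will first be summarised and compared. It sets no minimum gap.
- **Model and test.** An intercept-only mixed model with a random clinician effect is fitted to the rate. "An intercept that differs significantly from zero will indicate further change in ISI score between 6 weeks and discharge".
- **Covariates.** "Models will also include age and sex and other baseline characteristics that may be found to impact time to discharge".

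Two other sections bear on this. Under Intervention, a sleep pattern is detected "usually within 7 days", after which weekly recommendations follow: "This process will be repeated for the next 4 to 6 weeks". Participation can also end when the patient stops using the app or the course is complete. Under Outcome measures, the battery containing the ISI is scheduled as follows: "The battery will be completed through the NOCTEM app at baseline, post-treatment, and again 3 and 12 months post-treatment".

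**The concern.** The formula and its label disagree on the unit, so whoever follows the text will report a number that is wrong by a constant. The denominator can be zero, and it can be small for patients who finish close to week 6. The description of the model leaves open which intercept carries the test. The outcome is a discharge ISI that the assessment schedule does not list, while the two follow-up ISI scores that are listed appear in no stated durability analysis.

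What is at stake is the reported size of further change after week 6 and, through the weighting and the choice of intercept, how far that estimate can be trusted. No primary hypothesis, sample size or error rate depends on it.

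**Working it through.** The plan gives no numerical result for this analysis, so there is no figure to reproduce. The formula is evaluated as printed.

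**1. Unit.** Weeks per month = 365.25 / 12 / 7 = 4.348. Take an ISI of 12 at week 6 and 9 at discharge in week 18 (illustrative values).
- Printed formula: (12 − 9) / (18 − 6) = 0.25, in points per week.
- Monthly rate: 0.25 × 4.348 = 1.087 points per month.

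Multiplying every rate by a constant scales the estimate and its standard error alike. In simulated data (set-up in step 5, without an age effect), the intercept is 0.140 per week or 0.610 per month, with t = 3.99 in both units.

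**2. When the denominator is zero or small.** Detection within about 1 week plus 4 to 6 weeks of recommendations puts the end of a course at about weeks 5 to 7, or earlier if detection is faster. At discharge week 6 the denominator is 6 − 6 = 0 and the rate is undefined. The documents give no distribution of discharge times, so how many patients fall near week 6 is unknown.

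**3. Discharge before week 6.** Suppose a steady improvement of 0.5 points per week and both scores taken at their true times. Discharge at week 4 then gives (x − (x + 1)) / (4 − 6) = +0.5, the same as for discharge at week 7 or 10. The sign is kept, but the value describes change before week 6, not after it.

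**4. Weighting.** If the ISI difference has a constant SD s, the rate has SD s / gap and variance s² / gap². The ratio of variances at gaps of 1 and 20 weeks is 20² = 400, and s cancels. With s = 4 points (assumed), the SD of the rate is:

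| Gap (weeks) | SD of rate (points/week) | Variance |
|---|---|---|
| 1 | 4.00 | 16.00 |
| 4 | 1.00 | 1.00 |
| 12 | 0.33 | 0.11 |
| 20 | 0.20 | 0.04 |

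The share of the variance of an unweighted mean that comes from the 1-week group depends on an assumed mix of gaps:
- Equal quarters: 16 / 17.15 = 93%.
- 10% at 1 week and 30% at each other gap: 1.6 / (1.6 + 0.3 × 1.151) = 82%.
- 5% at 1 week, the rest equal: 0.8 / (0.8 + 0.3167 × 1.151) = 69%.

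If instead the variance of the difference grows in proportion to the gap, the 1-week to 20-week ratio falls from 400 to 20. The equal-quarters share becomes 1 / (1 + 0.25 + 0.083 + 0.05) = 72%.

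**5. Which intercept.** With raw age in the model, the intercept is the expected rate at age 0 and the reference sex. One data set per scenario was simulated: 24 providers with 36 patients each, as in the plan. Assumed were mean age 34 (SD 9), a mean rate of 0.10 per week, a provider SD of 0.15 and a residual SD of 0.5. Mixed-model intercepts:

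| Age effect per year | No covariates | Raw age and sex | Centred age and sex |
|---|---|---|---|
| 0 | 0.140 (t 3.99) | 0.176 (t 2.27) | 0.140 (t 3.99) |
| 0.01 | 0.093 (t 2.51) | −0.199 (t −2.62) | 0.093 (t 2.52) |

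The second row agrees with direct arithmetic: 0.10 + 0.01 × (0 − 34) = −0.24 is the rate expected at age 0.

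**6. Schedule.** The battery schedule under Outcome measures lists baseline, post-treatment, and 3 and 12 months post-treatment. A discharge assessment appears only in the durability paragraph. In the main statistical section, the ISI models use baseline and 6 weeks, and the 3- and 12-month comparisons concern provider reach, adoption and sustainability.

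**The case against.** The strongest defence is that this is an exploratory analysis in a condensed article. Discharge times are to be summarised and compared, and their variability is to be taken into account. Coding of covariates is normally left to an analysis plan. The intercept-only model comes first, and the covariate sentence can be read as describing adjusted models fitted afterwards. Participation may also run to the end of the project, so gaps could be long for many patients. Much of this stands, and it limits the point to the text as printed.

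Four stronger readings are tempting, and the documents do not support them.

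- **That discharge before week 6 reverses the sign.** With scores at their true times, numerator and denominator both flip. Reversal needs a nominal 6-week score taken before an earlier discharge: a score of 13 at week 4 and 12.5 at discharge in week 5 gives (13 − 12.5) / (5 − 6) = −0.5 despite improvement. The text does not say that scores are handled this way.
- **That covariates make the intercept meaningless.** This holds only if uncentred covariates enter the tested model. With centred ones the unadjusted result returns.
- **That the unit error invalidates the test.** It changes only the reported size.
- **That the result is mostly noise.** The 69% to 93% shares rest on assumed gap mixes that the documents do not supply.

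The article's silence on an analysis of the 3- and 12-month ISI also does not show that those data will be ignored, only that no stated durability analysis uses them.

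The defence does not remove the mismatch between formula and label, the zero denominator or the unscheduled outcome. Taking elapsed time into account is promised, but the only mechanism stated for the rate is the division that creates the short-gap problem.

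**Conclusion.** The point holds as an error in a stated formula, with minor severity.

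- **Certain from the text:** a weekly rate is labelled monthly, so reported values would be too small by a factor of about 4.35. The ratio is undefined at discharge week 6, with no rule for earlier discharge. The discharge ISI is absent from the battery schedule.
- **Conditional:** short gaps weigh heavily in an unweighted analysis. The variance ratio between 1 and 20 weeks is 400 if the SD of the ISI difference is constant, and 20 if its variance grows with the gap. The effect on the trial's estimate depends on discharge times that are not given.
- **Ambiguous:** the tested intercept equals the mean rate only if the covariates are centred or the test stays with the unadjusted model. The text fixes neither.

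**What to change.** **Minimum.** Divide by (discharge week − 6) / 4.35, or relabel the rate as per week. Restrict the analysis to patients discharged after week 6 and say that the estimate describes those patients only. State that the test belongs to the unadjusted model, or centre the covariates.

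**Preferred.** Do not form individual ratios. Take the ISI values from week 6 onward (6-week, 3- and 12-month, plus discharge if it is collected) as outcomes in a mixed model on actual time since week 6, with patient and provider random effects and centred covariates. Test the time effect and report it per month, stating the direction, because a falling ISI is improvement and the present ratio is positive for improvement. This removes the unit error, the zero denominator and the ambiguous intercept, and it no longer lets short gaps carry undue weight.

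If a discharge ISI is intended, add it to the battery schedule. The Intervention section has the app disabled once a patient leaves the provider's care, and the battery is completed through the app. The sponsor should therefore confirm that the 3- and 12-month scores can be obtained after that point.

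**Cost.** Analysis wording, and one line in the schedule if a discharge ISI is kept. The sample size and the primary analyses do not change.
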